#### Details of outcome measures

Clinical assessment including anthropometry, blood sample provision and bioelectrical impedance (BIA) or dual x-ray absorptiometry (DXA) scans will be carried out at the research sites as described in Table 5. Height (cm) will be measured using a wall mounted stadiometer and weight (kg) will be measured using electronic scales. Body composition to include fat mass and lean mass in kg and as %body weight will be measured using either DXA and/or BIA, depending on what is available at the site. Waist circumference (cm) will be measured using a non-stretch tape and blood pressure (BP) (mmHg) will be measured using an automated blood pressure machine. The mean of three measurements of height, weight and waist circumference will be used for these outcome variables. For BP, three measurements will be recorded and the mean of the second and third measurements will be used. Adherence to the dietary pattern will be measured during the intervention period using a 24-h dietary recall and a FFQ (25). The FFQ includes additional questions specifically related to the dietary pattern of interest. The dietary pattern will be assessed using the FFQ data to create a Mediterranean diet adherence score based on the number of serves of olive oil, vegetables, fruit, breads & cereals, legumes, nuts, fish and seafood, eggs, poultry, dairy foods, red meat and sweets that the participants consume (33). A fecal sample will be collected from index participants for future microbiome analysis (Table 5).

**Table 5 tab5:** Schedule of measurements for index participants.

Study period timepoints								
	Eligibility	Enrolment	Intervention and follow up					
	Visit 1 Screening	Visit 2 Baseline Enrolment	Phone contact	Email Contact	Visit 3a Control only	Visit 3b	Visit 4	Visit 5
RCT1 control group		Week 0			Week 12	Week 24	Week 36	Week 64
RCT1 intervention group			Week 2	Week 6		Week 12	Week 24	Week 52
Eligibility screen	✓							
Informed consent	✓							
Medical history	✓							
Education about RCT 1 and RCT 2		✓						
Questionnaires								
Otago short-form FFQ		✓			✓	✓	✓	✓
24 h dietary recall		✓		✓	✓	✓	✓	✓
IPAQ Physical activity		✓			✓	✓	✓	✓
Kaupapa Māori Wellbeing questionnaire		✓			✓	✓	✓	✓
Three factor eating questionnaire		✓			✓	✓	✓	✓
Gastrointestinal symptom rating scale		✓			✓	✓	✓	✓
Self-Evaluation COM questionnaire		✓			✓	✓	✓	✓
Impact evaluation for nutrition and behavior change support					✓	✓	✓	✓
SF-36 quality of life		✓			✓	✓	✓	✓
Assessments								
Height	✓							
Clinical measurements^a^	✓	✓			✓	✓	✓	✓
Body composition		✓			✓	✓	✓	✓
Current medications	✓	✓		✓	✓	✓	✓	✓
Adverse events			✓	✓	✓	✓	✓	✓
Fasting blood samples ^b^	✓	✓			✓	✓	✓	✓
Fecal sample		✓			✓	✓	✓	

^a^Weight, waist circumference, height, blood pressure in triplicate. ^b^HbA1c, fasting glucose, lipids and metabolites and hormones related to metabolic health Household/whanau members will attend visits 2, 3a/3b, 4, and 5.

A number of sub-studies may be undertaken which include consumer insights including that of Pacific island participants; mixed meal tolerance tests; use of a phone application for the measurement of dietary intake; fecal microbiome analyses. Details of these sub-studies will not be described in this paper.

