### Control arm for RCT 1; usual dietary intake and lifestyle

Participants allocated to the control arm will continue their usual lifestyle and diet for 12-weeks. Nutritional education and social support will not be provided. At the end of this 12-week period, they will receive the intervention package described above, for 12-weeks.

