### Assignment of interventions

#### Allocation sequence generation in RCT 1 and in RCT 2 (Spirit 16a)

Index participants and their household/whānau will be block randomized into RCT 1 at site level to either start the intervention package or continue usual dietary intake for 12 weeks. If there is a second person within the household/whānau who meets the criteria for an index participant, they will be allocated to the same arm as the first index participant, where applicable. Index participants will be randomized using a computer-generated sequence. Household/whānau members will be randomized to the same arm as their corresponding index participant. Index and household/whānau participants will all be randomized once their data have been collected at Visit 2. It is not possible to blind index participants or their household/whānau members to the intervention in RCT 1. Nor is it practical to blind study staff collecting data, however the principal investigator, study statistician and the laboratory team will remain blinded throughout the study and analysis period. Participants will be informed of which arm of RCT 2 they are randomized to after they have completed the RCT 1 intervention.

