### Statistical analyses

The primary analysis will be conducted according to the intention to treat principle. Appropriate data descriptions and plots will be used for all variables. Change from baseline variables will also be described as paired differences but, in general, baseline values of response variables will be used as covariates in analyses rather than analyzing change from baseline. For RCT 1 and RCT 2 and for the index participants, the primary analysis for the primary outcome variable will be Analysis of Covariance (ANCOVA) with the baseline value of the MetSSS as a continuous covariate and the randomized treatment as the main explanatory variable. This strategy will also be used for all continuous outcome variables with the appropriate baseline value of any specific outcome variable as the covariate. The baseline measurement will be just before the relevant randomization. Normal distribution assumptions for residuals will be checked for models of continuous outcome variables and if these are badly violated transformations, such as a logarithm transformation, will be used. For some variables, outlined in Table 4, it is already established that the logarithm transformation is likely to be appropriate. Where appropriate transformations cannot be identified a rank-based procedure, the Mann–Whitney test with the Hodges-Lehmann estimator of location difference, will be used. For the primary outcome variable, the MetSSS, a sensitivity analysis will be a secondary analysis adjusting for possible confounding by important explanatory variables that may have not been evenly distributed by the randomization. These will be as a composite categorical variable for whether medication was changed for any of blood pressure control, glucose management, or lipid control; and separately, for physical activity assessed by the international physical activity questionnaire score. Analysis will be by ANCOVA with these confounding variables in addition to the baseline MetSSS and randomized treatment. Another secondary analysis will be to explore if randomized treatment allocation is associated with different effects in subgroups; using an appropriate treatment by subgroup interaction models. These subgroups are: age, sex, baseline diet adherence score, household size, and whether a household has children. For the continuous variables the analysis of the interaction will be on the continuous scale but for illustrative purposes, and for use in a Forest-like plot, will also be estimated for the first and third quartile of the continuous predictor distribution. Another important secondary analysis will be of all participants treating each household as a cluster and using a Mixed Linear model with baseline measurement and randomized treatment as fixed effects, and household clusters as random effects. If in the event there are very few clusters, the random effect may not be estimable and then this will be equivalent to ANCOVA. The Intraclass correlation coefficient for the clustering effect will be estimated directly from the variance components in the mixed linear models, should a cluster effect be estimable. Categorical and ordinal variables will be analyzed by logistic regression, the latter corresponding to ordinal regression, for the individual participant analysis, and by a Generalized Mixed Linear Model for all participants. There may be other effect modifiers that we will consider but these will be outlined in the Statistical Analysis Plan.

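### Table 5 schedules adverse event enquiries three times in the intervention arm and once in controls during the 12 weeks of RCT 1, which would tilt any between-arm adverse event summary (minor)

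*Protocol article*

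**What the plan says.** Table 5 (Details of outcome measures) lists the visits and contacts for index participants, with one row of weeks per arm. Only the row labelled "RCT1 intervention group" has entries in the phone and email columns. Read across, the rows are:

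- Intervention: "RCT1 intervention group Week 2 Week 6 Week 12 Week 24 Week 52". Weeks 2 and 6 fall in the phone and email columns, and week 12 is Visit 3b.
- Control: "RCT1 control group Week 0 Week 12 Week 24 Week 36 Week 64". The phone and email cells are blank, and the first entry after randomization is Visit 3a at week 12.

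In the assessment rows, "Adverse events" is ticked at the phone contact, the email contact and Visits 3a, 3b, 4 and 5. "Current medications" is ticked at Visits 1 and 2, the email contact and Visits 3a, 3b, 4 and 5, but not at the phone contact. The 24 h dietary recall is also ticked at the email.

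The control arm section fixes the comparison period: "Participants allocated to the control arm will continue their usual lifestyle and diet for 12-weeks". The allocation section says: "It is not possible to blind index participants or their household/whānau members to the intervention in RCT 1". It adds that blinding the staff who collect data is not practical. Under Statistical analyses, a sensitivity analysis of MetSSS adjusts for "whether medication was changed for any of blood pressure control, glucose management, or lipid control".

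**The concern.** The number of adverse events reported on enquiry depends on how often people are asked and how far back they must remember. If one arm is asked more often and over shorter intervals, it will tend to report more events without any real difference. Here participants and data collectors know the allocation, and the more closely questioned arm is the one on the new diet, so the tilt is against the intervention. Once the data are in, the only way to equalise them is to set the extra enquiries aside. That choice is better stated beforehand than made after the counts are known.

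Medication enquiries differ in the same way, though less. This matters because medication change is a covariate in the sensitivity analysis of the primary outcome, and the article does not say which enquiries define it.

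**Working it through.** **Step 1: count the scheduled enquiries.** Crossing the two week rows of Table 5 with the assessment rows gives, from randomization to week 12:

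| Item | Intervention | Control |
|---|---|---|
| Adverse events | 3 (weeks 2, 6, 12) | 1 (week 12) |
| Current medications, after baseline | 2 (weeks 6, 12) | 1 (week 12) |
| 24 h recall, after baseline | 2 (weeks 6, 12) | 1 (week 12) |

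The longest interval to be recalled for adverse events is 6 weeks in the intervention arm (week 6 to week 12) and 12 weeks in controls.

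**Step 2: check for a misread table.** Week 0 is printed only in the control row although both arms attend Visit 2, so it is probably a merged cell and blank cells need care. A merged value would land in the upper row, which is the control row. Weeks 2 and 6 stand in the lower row, so they read as specific to the intervention arm. The data collection section mentions phone calls but does not say that controls receive them. No other section gives controls matching contacts, either in the usual-diet period or at weeks 2 and 6 of their delayed intervention (study weeks 14 and 18).

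**Step 3: illustrate the size for adverse events.** The protocol gives no figure, so this step rests on assumptions: events occur uniformly over 12 weeks, the true rate is equal in both arms, and the chance that an event is still reported decays exponentially with half-life h until the next enquiry. With k = ln 2 / h, the fraction captured is

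(1/12) × Σ (1 − exp(−kL)) / k,

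summed over the intervals L between enquiries: 2, 4 and 6 weeks for intervention, and a single interval of 12 weeks for control.

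For h = 4 weeks, k = 0.1733:

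- Intervention: (1.690 + 2.885 + 3.730) / 12 = 8.306 / 12 = 0.692
- Control: 5.049 / 12 = 0.421
- Ratio: 1.64

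| Half-life | Intervention | Control | Apparent rate ratio |
|---|---|---|---|
| 4 weeks | 0.692 | 0.421 | 1.64 |
| 8 weeks | 0.825 | 0.622 | 1.33 |
| 12 weeks | 0.878 | 0.721 | 1.22 |

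Under this model the ratio exceeds 1 for any finite half-life. Its size depends on the half-life chosen.

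**Step 4: medications.** The recall model does not apply here, because the item is a list of current drugs. Both arms have a list at Visit 2 and another at week 12. If change means a difference between those two lists, it is derived identically in both arms. The week 6 email adds something in one arm only if a change made and reversed before week 12 is counted, or if changes are tallied at every contact. The article does not say which definition applies.

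**The case against.** The strongest case against is that no planned result is affected. Adverse events are not an outcome in Table 4, and Statistical analyses sets out no comparison of them by arm. The Safety section speaks only of reporting serious events to the ethics committee. Gastrointestinal symptoms, a likely tolerability question in a diet trial, are measured by a rating scale at baseline and week 12 in both arms. One recall decay rate is applied to all events, although serious ones are unlikely to be forgotten. All of this stands, and it keeps the point minor. It does not remove it: the schedule is stated, it differs by arm, and it would tilt a by-arm adverse event table if one is produced.

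Three stronger readings are tempting but unsupported:

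- **That the primary result is biased.** MetSSS is measured at the same times in both arms. The medication covariate enters only a sensitivity analysis, and the documents do not establish that it is recorded differently by arm.
- **That the additional contact is itself a flaw.** RCT 1 compares a package that includes support with usual care, so some difference in contact is intended.
- **That the extra 24 h recall is an unexplained imbalance.** The outcome measures section uses the recall to measure adherence during the intervention, which accounts for it. That purpose does not account for asking about adverse events and medications in one arm only.

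It is also fair that question wording and tabulation rules often sit in the full protocol or analysis plan. The point here is the printed schedule, not their absence from the article.

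**Conclusion.** The point holds as a minor one. On the schedule as printed, RCT 1 asks about adverse events three times in one arm and once in the other, and about medications after baseline twice against once. Any between-arm summary of adverse events that uses all enquiries would lean towards more reported events in the intervention arm. An apparent rate ratio of 1.2 to 1.6 illustrates the possible size with no true difference; it rests on the assumed half-life of 12 to 4 weeks, uniform events and a single decay rate, and it does not estimate bias in any planned analysis. The count also assumes that the phone and email cells belong to the intervention row alone, which is the more natural reading of the table.

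**What to change.** Choose one of two changes.

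1. **Match the enquiries.** Give controls the same brief adverse event and medication enquiry at weeks 2 and 6 of the usual-diet period, and show it in the control row of Table 5. No extra 24 h recall is needed. With 200 index participants and equal allocation assumed, this is about 100 controls with two short contacts each, so about 200 contacts using existing forms. It adds a little contact to a usual-care arm.

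2. **Restrict the comparison.** State that RCT 1 between-arm summaries of adverse events use only the week 12 enquiry (Visit 3a for controls, Visit 3b for intervention), with the same question and recall period in both arms. State also that medication change is defined in both arms by comparing the Visit 2 and week 12 lists. This costs a sentence or two. The week 2 and week 6 reports would then be described for the intervention arm only and left out of the comparison.

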### Participant timeline (Spirit 13)

The duration of the study is 52-weeks after the intervention component of RCT 1.

### Sample size (Spirit 14)

The sample size uses a clinically important difference of 0.4 for the MetSSS score based on detecting a ‘moderate’ effect size. This is because the MetSSS score was designed to represent the total number of standard deviations different for an overall risk factor profile for poor cardiovascular outcomes (19, 34). The standard deviation for the MetSSS for the calculation, 0.83, was derived from a large Auckland-based cohort study of these risk factors in a similar sample to that for recruitment (20). A t-test based sample size calculation used 90% power and a two-sided type I error rate of 0.05 was for 184 total participants and increased to 200 index participants to allow for a 10% non-completion rate. A smaller effect size is likely to be detectable by using baseline MetSSS as a co-variate in an ANCOVA.

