**Methods and analysis:**

This is a multi-center, three-stage trial with two parallel group superiority randomized controlled trials (RCTs), and a longitudinal cohort study embedded within the trial design. The first RCT (RCT 1) is a comparison of the NZMedDiet pattern compared to usual diet for 12 weeks. The Behavior Change Wheel was used to select and implement strategies to support participant adherence to the NZMedDiet, such as web-based nutrition education on healthy shopping and cooking. The second (RCT 2) compares online social support to no online social support for 12 weeks, administered to participants immediately following RCT 1. The third stage is a longitudinal cohort study where all participants are followed from the beginning of their start of the active intervention for 12 months in total. The primary outcome measure for each stage is the metabolic syndrome severity score (MetSSS). The duration of enrolment is 12–15 months. The total recruitment target is 200 index participants and their household/whānau members who participate with them, and the primary analyses will be intention to treat on index participants.

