### Trial design (Spirit 8)

This is a multi-center, three-stage trial, with two randomized controlled trials (RCTs); both parallel group superiority trials, and a longitudinal cohort study. The first RCT (RCT 1) compares the effect of Mediterranean dietary pattern incorporating high quality New Zealand foods (NZMedDiet pattern) to usual diet on MetSSS, a marker of cardiometabolic health for 12-weeks. The intervention in RCT 1 includes elements of behavior change science including the provision of food, recipes, weekly meal plans, access to web-based nutrition education and opt-in online social support. From here on within the manuscript ‘RCT 1 intervention’ is referred to as a package including these described aspects. The second RCT (RCT 2) compares the opt-in online social support, to no online social support with an outcome assessment 12 weeks after the second randomization (Figure 1). Those participants who were originally randomized to the control group in RCT 1 will be given the RCT 1 intervention before the second randomization. After the second randomization, both groups continue to have access to the bespoke study website housing nutrition information and education. The third stage is a longitudinal cohort study where all participants are followed for 12 months from the start of the dietary intervention. The trial design is summarized in Figure 1 (Spirit 8).

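### Recruiting 200 to secure 184 completers allows for 8% non-completion, not the stated 10%; the effect on power is about half a percentage point

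*Protocol article*

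**What the plan says.** All the inputs are in the protocol article, under Sample size (Spirit 14). The target difference: "The sample size uses a clinically important difference of 0.4 for the MetSSS score". The spread: "The standard deviation for the MetSSS for the calculation, 0.83, was derived from a large Auckland-based cohort study". The test and error rates: "A t-test based sample size calculation used 90% power and a two-sided type I error rate of 0.05". The result and its inflation: it "was for 184 total participants and increased to 200 index participants to allow for a 10% non-completion rate". The section ends by noting a likely gain from adjustment: "A smaller effect size is likely to be detectable by using baseline MetSSS as a co-variate in an ANCOVA".

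This is the only sample size calculation in the article. It names neither the RCT it serves nor the visit at which the 10% is counted. Under Statistical analyses, the primary analysis of MetSSS in both RCTs is ANCOVA, with the value just before the relevant randomization as covariate.

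**The concern.** The inflation step and its stated rationale sit in one sentence and do not agree. If a tenth of 200 index participants do not complete, 180 remain, and that is below the 184 that the same sentence says are needed. A reader who takes the sentence at face value will believe that 90% power is protected against 10% loss, when the protection ends at 8%.

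Little is at stake: the accuracy of a stated design figure that will probably be repeated in the trial report. The recruitment target is not in question.

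**Working it through.** **Inputs.** Difference 0.4, SD 0.83, power 90%, two-sided alpha 0.05, 184 evaluable, 200 recruited, 10% non-completion, all from Sample size (Spirit 14). The allocation ratio is not stated; 1:1 is assumed, and it reproduces 184.

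**Step 1: reproduce 184.** Standardized difference d = 0.4/0.83 = 0.482.
- Normal approximation: n per arm = 2 × [(1.960 + 1.282) × 0.83/0.4]² = 90.5, so 91 per arm and 182 in total.
- Noncentral t, with noncentrality d × √(n/2) and 2n − 2 degrees of freedom: 91 per arm gives 89.9% power and 92 per arm gives 90.2%. The smallest adequate size is 92 per arm, 184 in total, which is the article's figure.

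**Step 2: check the allowance.**
- Completers at 10% loss: 200 × 0.90 = 180, which is 4 fewer than 184.
- Loss that 200 can absorb: 1 − 184/200 = 8.0%.
- Recruitment needed for 10% loss: 184/0.90 = 204.4, so 205 (206 for equal arms).
- The cruder rule of adding 10%: 184 × 1.10 = 202.4, so 203.

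Neither convention takes 184 to 200. The normal-approximation total does come close (182 × 1.10 = 200.2), which may be where 200 came from. That is conjecture, since 182 does not appear in the article.

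**Step 3: size of the effect.** Power for a difference of 0.4, noncentral t, no adjustment:

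| Completers | Power |
|---|---|
| 184 | 90.2% |
| 180 | 89.5% |

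At 180 the difference detectable with 90% power is about 0.404 instead of 0.40.

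**Step 4: baseline adjustment.** ANCOVA reduces the residual SD to 0.83 × √(1 − r²), where r is the correlation between baseline and follow-up MetSSS. The article gives no r, so a range is shown, at 180 completers:

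| r | Power |
|---|---|
| 0.15 | 90.2% |
| 0.3 | 92.1% |
| 0.5 | 96.0% |
| 0.7 | 99.4% |

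A correlation of about 0.15 is enough to return to 90%.

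**Step 5: what could be said about RCT 2.** Three attrition scenarios, each an assumption, with the same difference and SD:
- 10% is the total loss up to the RCT 2 outcome: 180 completers, 89.5% unadjusted.
- Two successive 10% losses in everyone: 200 × 0.9 × 0.9 = 162 completers. Power is 86.2% unadjusted, 89.2% at r = 0.3 and 94.1% at r = 0.5.
- 10% lost in every 12-week phase, with the delayed arm passing through three phases and the immediate arm two: 100 × 0.9³ + 100 × 0.9² = 72.9 + 81 = 153.9, about 154 completers. Power is 84.4% unadjusted.

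These results span both sides of 90%, according to inputs that the article does not give.

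**The case against.** The best defence is that the slip has no practical consequence. The target of 200 is only 2.5% below 205, the unadjusted power lost against 90% is about half a point, the article itself says that adjustment is likely to make a smaller effect detectable, and ANCOVA is the planned primary analysis. All of that stands, and it is why the point is minor. It does not make the sentence right: 200 is described as covering 10% loss from 184, and it does not.

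A reader might go further and infer that 90% power fails to carry over to RCT 2. RCT 2 shares the primary outcome ("The primary outcome measure for each stage is the metabolic syndrome severity score (MetSSS"), and its entrants have already passed through earlier phases: "Those participants who were originally randomized to the control group in RCT 1 will be given the RCT 1 intervention before the second randomization". The article does not support that as a shortfall, for four reasons:
- The 10% is tied to no stage. If it covers losses up to the RCT 2 outcome, the answer is again 89.5%.
- No 90% power is claimed for RCT 2, and the Introduction makes continued online social support a secondary objective.
- Figures such as 86.2% describe an unadjusted t-test, while ANCOVA is planned for RCT 2 too.
- The 0.4 is presented as a clinically important difference on the MetSSS scale, not as the expected effect of the food package, so its use for a narrower contrast is not an error.

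A separate RCT 2 power statement may also sit in the full protocol or the SAP, neither of which is shown.

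**Conclusion.** The point holds as an arithmetic correction of minor size. The 184 is right. The 200 allows for 8.0% non-completion rather than 10%, and at 10% loss it leaves 180 completers and 89.5% power by unadjusted t-test. This rests on 1:1 allocation, independent index participants, and the article's own difference and SD. The planned baseline adjustment is likely to more than recover the difference, although the size of that gain depends on a correlation that the article does not state.

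Nothing here shows that either RCT is underpowered, and the recruitment target does not need to rise.

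**What to change.** Keep 200 and change the sentence. Either say that 200 index participants allow for 8% non-completion at 90% power, or say that with 10% non-completion the expected 180 completers give 89.5% power, in each case before the ANCOVA adjustment for baseline MetSSS.

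As an optional clarification, say which RCT and which visit the non-completion rate refers to. If a power figure for RCT 2 is added, give it as a range over stated attrition and baseline correlation, as in Step 5.

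The cost is one reworded sentence and a marginally less favourable stated figure. Recruitment, design and analysis do not change.
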